## Measures

A description of each quantitative measure used at each assessment is provided in Table 2, and a timeline of assessments is provided in Table 3. Most measures have demonstrated good reliability and validity in Mandarin-speaking populations (Table 2). Surveys that do not have validated Chinese translations will be translated and checked for quality by qualified translators using an established five-step process for translation and evaluation developed by Forsyth et al. [39]. All measures will be administered either by phone or videoconference by trained bilingual research staff and entered into REDCap, a secure web platform for electronic data capture.

**Table 2 Tab2:** List of assessments

Measure Title	Time Points Used	Outcome	Description of Measure
Demographic and Clinical Characteristics	T1 (Baseline)	n/a	Age (years), gender, race, ethnicity, education, preferred language, level of English proficiency, country of origin, immigration length, frequency of revisiting birthplace, employment status, household income, marital status, household size, religious/spiritual beliefs, health insurance status, most recent cancer diagnosis, and current cancer treatment received
Digital Health Care Literacy (DHCL) [40]	T1 (Baseline)	n/a	The DHCL is a brief (3-item), face valid measure of one’s confidence in the ability to use technological programs or services and the ability to independently troubleshoot technical issues. Cronbach’s α = 0.90 [36]
Feasibility	T8 (Post-intervention)	Primary	Feasibility will be assessed via attendance logs and defined as ≥11 out of 15 participants completing ≥5/6 sessions
Acceptability	T8 (Post-intervention)	Secondary	A 20-item, investigator-initiated, face-valid survey to assess participants’ satisfaction with the intervention, mode of delivery (via RSMI or bilingual interventionist) and effects of treatment (i.e., whether the intervention was helpful). Acceptability will be scored by calculating the percentage of positive (“agree”) responses
Therapeutic Alliance (WAI-S) [41]	T2, T3, T4, T5, T6, T7 (Post-sessions 1–6)	Secondary	The Working Alliance Inventory-Short Form (WAI-S) is a 12-item self-report scale of therapeutic alliance with 2 forms: one for the client, and one for the interventionist. Cronbach’s α = 0.86. [42]*
MCP-Ch Content Comprehension	T8 (Post-intervention)	Secondary	A 10-item, face-valid, investigator-initiated questionnaire. These multiple-choice items assess a participant’s understanding of MCP concepts presented in the MCP-Ch program
Clinically significant interpreting errors in MCP-Ch Session 1	T8 (Post-intervention)	Secondary	The number and nature of clinically significant interpreting errors made in MCP-Ch Session 1 (RCMI, RSMI arms only) will be assessed using an error analysis tool developed by Gany et al. [21] For more details, see Data analysis plan, objective #2
Credibility/Expectancy Questionnaire (CEQ) [43]	T2 (Post-session 1)	Exploratory	The CEQ is a 6-item questionnaire, half of which relates to the subscale of credibility (i.e., how believable, convincing, and logical the treatment is) and the other half to expectancy (i.e., the improvements the patient believes will be achieved). *r* = 0.85. [49]
Distress Thermometer (DT) [44]	T1 (Baseline), T8 (Post-intervention)	Exploratory	The Distress Thermometer (DT) is a single-item scale used to screen cancer patients for the presence of psychological distress with a 0–10 range. *r* = 0.80 [45].*
Spiritual Well-Being Scale (FACIT-Sp) [46]	T1 (Baseline), T8 (Post-intervention)	Exploratory	The Functional Assessment of Chronic Illness Therapy—Spiritual Well-Being Scale (FACIT-Sp) is a 12-item self-report instrument assessing the spiritual well-being of people with chronic and/or life-threatening illnesses. It has three subscales: Peace, Meaning, and Faith. Cronbach’s α = 0.89 [47]*
McGill Quality of Life Questionnaire (MQOL) [48]	T1 (Baseline), T8 (Post-intervention)	Exploratory	The McGill Quality of Life Scale (MQOL) is a 16-item quality of life self-report measure for people with life-threatening illness. It is composed of 4 subscales: physical symptoms, psychological symptoms, outlook on life, and meaningful existence. Cronbach’s α = 0.87 [49]*
Hospital Anxiety and Depression Scale (HADS) [50]	T1 (Baseline), T8 (Post-intervention)	Exploratory	The 14-item Hospital Anxiety and Depression Scale (HADS) measures both anxiety and depression symptoms. Cronbach’s α = 0.93 [51]*
Meaning in Life Questionnaire (MLQ) [52]	T1 (Baseline), T8 (Post-intervention)	Exploratory	The MLQ is a 10-item measure of meaning-in-life with 2 factors: Presence and Search. Cronbach’s α = 0.84-0.88 depending on subscale [53].*
Beck Hopelessness Scale (BHS) [54]	T1 (Baseline), T8 (Post-intervention)	Exploratory	The Beck Hopelessness Scale (BHS) is a 20-item true–false self-report measure of participants’ degree of pessimism and hopelessness. Cronbach’s α = 0.85 [55].*
Weekly Session Rating and Telehealth Evaluation	T2, T3, T4, T5, T6, T7 (Post-sessions 1–6)	n/a	A 10-item investigator-initiated session rating and telehealth evaluation assessing participant impressions of each intervention session, as well as any technical difficulties with videoconferencing or telephone delivery
Telehealth Usability (TSQ) [56]	T8 (Post-intervention)	n/a	The 14-item Telemedicine Satisfaction Questionnaire evaluates patient-reported usefulness, ease of use, effectiveness, reliability, and satisfaction of how telehealth delivery of an intervention functioned in comparison to a traditional in-person encounter. Cronbach’s α = 0.93 [52]
Exit Survey	T8 (Post-intervention)	n/a	A 4-item, investigator-initiated survey to collect participant feedback for program improvement

*Reliability statistics from studies of validated Chinese translations

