**Methods:**

A total of 45 participants will be randomly assigned to one of 3 arms (*n* = 15 RCMI, *n* = 15 RSMI, and *n* = 15 bilingual provider) to receive 6 counseling/psychotherapy sessions. Feasibility and acceptability of the interpreting modalities (RCMI, RSMI) will be evaluated through self-report assessments. Secondary outcomes will include therapeutic alliance, MCP-Ch content comprehension, and clinically significant interpreting errors across the interpreting (RCMI, RSMI) arms. Semi-structured interviews with a purposively sampled subset of patients, their interventionists, and interpreters (if applicable) across all 3 arms will assess potential barriers and facilitators to successful interpreter-mediated communication and outcomes.

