The majority of patients with LEP who access mental health care do so through medical interpreters, given a national shortage of bilingual mental health professionals [19]. Typically, medical interpretation is consecutive (interpreting is provided once a speaker has finished speaking) [20]. RSMI or “United Nations-style” interpreting is similar to a voice-over and is provided remotely by trained medical interpreters [20]. RSMI is likely superior to consecutive interpreting methods due to increased efficiency [21, 22], fewer clinically significant medical errors [21, 22], and enabling a more private and dyadic clinical encounter [21, 23]. By contrast, the most commonly employed interpreting strategy, Remote Consecutive Medical Interpreting (RCMI), can interfere with the collaborative relationship between patient and therapist (i.e., therapeutic alliance) [24], one of the most robust predictors of psychosocial intervention outcomes [25]. In addition, consecutive interpreting can impede the natural flow of communication, as interpreters pace their interlocutors. Yet to our knowledge, RSMI has not yet been studied in the telemental health context; a systematic review on the use of interpreters in mental health found no quantitative studies on interpreter accuracy nor on the influence of interpretation modes on the therapist–patient relationship [26].

To address these limitations, INTERPRET-PSY is a mixed method, explanatory sequential (QUANT qual), 3-arm pilot randomized controlled trial (RCT) developed to determine whether RSMI is feasible and acceptable in comparison to usual care (RCMI) and “gold standard” care (bilingual provider) in delivering psycho-oncology counseling to Mandarin-speaking Chinese cancer patients with LEP.

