## Outcomes

The first goal of INTERPRET-PSY is to determine the feasibility of using RSMI and RCMI to deliver a manualized, culturally adapted counseling intervention to LEP cancer patients. Participants will be deemed not evaluable for feasibility if they drop out prior to Session 6 due to non-intervention related issues (e.g., progression of cancer or death). These non-evaluable participants will be replaced and reasons for dropout tracked. A determination of feasibility for RSMI/RCMI (*primary outcome*) will be met if *n* = 11 complete treatment (a comparable 67% MCP completion rate was achieved in [name] original MCP trial [35]), defined as completing 5 out of 6 sessions (i.e., ≥11 out of 15 participants completing ≥5/6 sessions). We will also calculate the observed recruitment rate, retention rate, participant satisfaction with treatment protocol (*secondary outcome*, scored by calculating the percentage of positive “agree” responses on a satisfaction survey), and telehealth usability in all 3 arms (RSMI, RCMI, bilingual provider). These outcomes will be measured quantitatively within 1 month following the intervention (T8) through a post-intervention assessment.INTERPRET-PSY also will assess the effect of interpreter-mediated delivery on counseling/psychotherapy process outcomes. This will be measured by comparing the RSMI and RCMI groups to the “gold standard” bilingual provider group at post-intervention assessment (T8), administered within 1 month following the intervention. Outcomes will include therapeutic alliance, MCP-Ch content comprehension, and the number and nature of clinically significant interpreting errors in MCP-Ch Session 1 (*secondary outcomes*); participants’ treatment expectancy, post MCP-Ch session 1 (T2); and distress, spiritual well-being, quality of life, anxiety and depression, meaning in life, and hopelessness (*exploratory outcomes*). We will also assess post-session ratings after each MCP-Ch session (T2, T3, T4, T5, T6, and T7).We will identify barriers and facilitators to successful interpreter-mediated delivery of MCP-Ch in semi-structured interviews with “extreme responders” in each of the 3 arms (i.e., participants who score especially high or low on therapeutic alliance, MCP-Ch comprehension, and/or acceptability). These will be assessed approximately 3 months post-intervention (T9).

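### Acceptability is scored as one percentage over counselling, delivery-mode and treatment-effect items, so it cannot show separately how patients rate the interpreting mode

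*Protocol article*

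**What the plan says.** The Methods part of the abstract sets the target: "Feasibility and acceptability of the interpreting modalities (RCMI, RSMI) will be evaluated through self-report assessments". The Background gives the trial's purpose as to "determine whether RSMI is feasible and acceptable in comparison to usual care (RCMI) and “gold standard” care (bilingual provider", in the delivery of counselling.

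Table 2 (Measures) describes the instrument as "A 20-item, investigator-initiated, face-valid survey to assess participants’ satisfaction" and lists three domains: "satisfaction with the intervention, mode of delivery (via RSMI or bilingual interventionist) and effects of treatment (i.e., whether the intervention was helpful". The number of items per domain is not given. The scoring rule in Table 2 is "Acceptability will be scored by calculating the percentage of positive (“agree”) responses". Outcomes, objective 1, calls the same secondary outcome "participant satisfaction with treatment protocol", "scored by calculating the percentage of positive “agree” responses on a satisfaction survey".

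The Interventions and Assignment of interventions sections give all arms the same six MCP-Ch sessions; what differs is how they are delivered. The Data analysis plan, objective 1, summarises acceptability in all three arms by frequencies and percentages, with no test and no threshold. Outcomes, objective 3, and Qualitative interviews (T9) use low or high acceptability as one of three criteria for choosing interviewees, beside therapeutic alliance and comprehension.

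**The concern.** Two of the three domains, the intervention and whether it helped, ask about a programme common to every arm. Only the mode-of-delivery items ask directly about the feature that randomisation varies. When all 20 items go into one percentage, a patient who valued the counselling but disliked the interpreting and a patient with the opposite view can receive the same score.

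Two uses of the score are affected. The first is the arm-by-arm summary that speaks to the acceptability half of the trial's question and is meant to inform the larger trial. The second is the choice of interviewees: a patient who disliked the interpreting but liked the counselling may not register as a low scorer on this criterion, although the interviews are meant to find barriers to interpreted communication. The other satisfaction instrument at T8, the telehealth usability questionnaire, compares telehealth with an in-person visit, so it does not supply a rating of the interpreting mode.

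**Working it through.** The plan states no power, threshold or expected value for acceptability, so there is no figure to reproduce.

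**Inputs from the article:** 20 items; three domains; one percentage of agreeing answers; the same counselling in all arms.

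**Assumed, because the article does not give them:** m, the number of mode items (5, 7 or 10), and the agreement rates.

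**Formula.** With agreement p_mode on the m mode items and p_other on the remaining 20 − m:

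overall score = [(20 − m) × p_other + m × p_mode] / 20

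The overall gap between two arms is then

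overall gap = (m/20) × gap on mode items + (1 − m/20) × gap on other items.

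**Case 1: other items equal between arms.** Take p_other = 0.90 in both arms, and p_mode = 0.90 in one arm and 0.50 in the other (a 40-point mode gap). The first arm scores 0.90 whatever m is. The second scores:

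| m | Overall score, second arm | Overall gap |
|---|---|---|
| 5 | (15 × 0.90 + 5 × 0.50)/20 = 0.80 | 10 points |
| 7 | (13 × 0.90 + 7 × 0.50)/20 = 0.76 | 14 points |
| 10 | (10 × 0.90 + 10 × 0.50)/20 = 0.70 | 20 points |

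**Case 2: other items also respond to the mode.** Keep the 40-point mode gap and assume a 20-point gap on the other items. The overall gap is 10 + 0.75 × 20 = 25 points (m = 5), 14 + 0.65 × 20 = 27 points (m = 7), or 20 + 0.50 × 20 = 30 points (m = 10). If the other items also differ by 40 points, the overall gap is 40 points and there is no dilution. So dilution requires that the other items differ less between arms than the mode items do.

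**One patient.** Someone who agrees with every other item and no mode item scores (20 − m)/20: 75% for m = 5, 65% for m = 7, 50% for m = 10. At m = 14 it would be 30%. Whether such a patient looks satisfied depends on the unstated split.

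**The case against.** There are four serious counter-arguments.

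- **The construct may be broader.** The Discussion parts of the abstract and of the main text speak of the acceptability of delivering counselling through the interpreting mode, and Outcomes, objective 1, speaks of satisfaction with the treatment protocol. A survey of programme, mode and helpfulness fits that. This stands, and is a good reason to keep the overall percentage. It does not remove the need to see the mode items separately, since the abstract also promises acceptability of the modalities themselves.
- **The other items may carry signal.** The Background argues that consecutive interpreting can disturb the alliance and the flow of conversation. If so, satisfaction and perceived helpfulness may move with the mode, and differences between randomised arms on those items are partly an effect of delivery. This stands, and makes the dilution conditional, as Case 2 shows.
- **Pooling is partly inferred.** An article may leave subscores to the full protocol. But this one states the scoring rule twice, each time as a single percentage, and Table 2 names subscales or factors for other instruments (CEQ, FACIT-Sp, MQOL, MLQ) and none here. A single percentage is the plain reading.
- **Other information bears on the mode.** Alliance, comprehension and interpreting errors are measured, and the interview guide asks about preference for consecutive or simultaneous interpreting. This lessens the harm. The interviews cover only about 6 patients per arm, however, and their selection depends partly on this score.

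A reader might go further and infer that the score mostly measures liking for the counselling, or that the plan could declare acceptable a mode that patients reject. The documents support neither. The item split is not given, and no threshold or rule exists by which a mode would be declared acceptable.

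**Conclusion.** The point holds in a limited form. As written, the acceptability score cannot separate satisfaction with the interpreting from satisfaction with the counselling, although the trial asks about the interpreting mode. That follows from the text without any assumption about the item split.

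The size of the dilution does rest on assumptions. With 5 to 10 mode items and equal agreement on the rest, a 40-point mode gap reads as 10 to 20 points. The loss is smaller if the other items also respond to the mode, and vanishes if they differ as much as the mode items do.

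The consequence is confined to a descriptive secondary outcome and one of three criteria for selecting interviewees. Acceptability plays no part in the progression criteria, and the primary feasibility outcome is untouched.

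**What to change.** In Table 2, in Outcomes, objective 1, and in the Data analysis plan, objective 1:

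1. Keep the overall percentage as the stated secondary outcome.
2. State which items belong to each domain, and pre-specify the percentage of positive responses on the mode-of-delivery items as a separate subscore, reported for RSMI, RCMI and the bilingual provider. Report the intervention and treatment-effect items as two further subscores.
3. State that conclusions about acceptability of the interpreting mode rest on the mode subscore.
4. In Qualitative interviews (T9), consider the mode subscore together with the overall score when identifying low and high acceptability.

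Replacing the overall percentage with a mode-only score is not needed. It would redefine a secondary outcome in an open-label trial that has been enrolling since March 2024, and the subscore meets the concern without that.

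No new items, patients or data are required. Enrolment is under way and the article requires prior IRB approval for prospective changes to outcomes, so the subscores should be submitted for approval and fixed before results by arm are examined. There are two drawbacks: a score on fewer items is noisier per patient, and some mode items may not be fully comparable in the bilingual arm, which has no interpreter. The report should say so.

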**Table 3 Tab3:**
[figure not shown]
SPIRIT timeline of assessments

Standard Protocol Items: Recommendations for Interventional Trials (SPIRIT) figure. *DHCL* Digital Health Care Literacy, *DT* distress thermometer, *FACIT-Sp* Functional Assessment of Chronic Illness Therapy - Spiritual Well-Being, *MQOL* McGill Quality of Life Questionnaire, *HADS* Hospital Anxiety and Depression Scale, *MLQ* Meaning in Life Questionnaire, *BHS* Beck Hopelessness Scale, *CEQ* Credibility/Expectancy Questionnaire, *WAI-S* Working Alliance Inventory-Short Form, *TSQ* Telehealth Satisfaction Questionnaire

### Screener

Twelve self-report items will assess eligibility (e.g., level of English proficiency, preferred language, age, Chinese ethnicity, cancer diagnosis and stage, and state of residence). In addition, 3 items (i.e., cancer diagnosis and stage, HSCT, and presence of cognitive impairment) require study staff to screen participants’ electronic medical record and, if needed, follow up with the patient’s physician for confirmation of eligibility.

### Pre-intervention/baseline assessment (T1)

Patients will be asked the following demographic and clinical characteristics: their age (years), gender, race, ethnicity, education, preferred language, level of English proficiency, country of origin, immigration length, frequency of revisiting birthplace, employment status, household income, marital status, household size, religious/spiritual beliefs, health insurance status, most recent cancer diagnosis, and current cancer treatment received. Participants will also respond to the following: Digital Health Care Literacy (DHCL) [40], Distress Thermometer (DT) [44], Spiritual Well-Being (FACIT-Sp) [46], Quality of Life (MQOL) [48], Anxiety and Depression (HADS) [50], Meaning in Life (MLQ) [52], and Beck Hopelessness Scale (BHS) [54]. 

### Post-session 1 only (T2)

Credibility/Expectancy Questionnaire (CEQ) [43]

### Post-session assessments (T2, T3, T4, T5, T6, T7)

Therapeutic Alliance (WAI-S) [41], Weekly Session Rating and Telehealth Evaluation

### Post-intervention assessment (T8) administered within 1-month post-intervention

Distress Thermometer (DT) [44], Spiritual Well-Being (FACIT-Sp) [46], Quality of Life (MQOL) [48], Anxiety and Depression (HADS) [50], Meaning in Life (MLQ) [52], Beck Hopelessness Scale (BHS) [54], Telehealth Usability (TSQ) [56], Acceptability, MCP-Ch Concept Comprehension, and Exit Survey

### Qualitative interviews (T9)

Approximately 27 (or until saturation) INTERPRET-PSY trial participants, interpreters, and interventionists will be invited to complete semi-structured interviews with study staff, via teleconference or phone. We estimate that interviewing ~6 participants per arm (~18 patients/participants), ~3 interpreters, and ~6 interventionists will be sufficient based on prior interview-based studies indicating metathemes can be identified in as early as 6 interviews and thematic saturation within 12 interviews [57]. Interviews will be conducted in Mandarin with patients/trial participants, in English with interventionists, and in Mandarin or English with interpreters (based on interpreter preference). The interviews will be approximately 45 min. Interviews will be conducted by study staff using a semi-structured guide with the following domains: (1) general feedback about their experiences with the INTERPRET-PSY study (i.e., for *patients/participants*, what they thought of the Mandarin-speaking abilities of their interventionist and/or interpreter; perceived relationship/rapport with their interventionist and/or interpreter; and their preferences for consecutive vs. simultaneous interpretation; for *interpreters*, their experience providing interpreting services and preferences for consecutive vs. simultaneous interpretation; for *interventionists*, their experience conducting psycho-oncology counseling and their preferences for consecutive vs. simultaneous interpretation) and (2) barriers and facilitators to remote interpreting implementation in the delivery of psycho-oncology care (i.e., barriers and facilitators to interpreter-mediated communication, the development of therapeutic alliance, and intervention delivery). To facilitate mixed methods integration, selection of patients/trial participants will be guided by quantitative results (i.e., low vs. high therapeutic alliance, low vs. high intervention comprehension, low vs. high acceptability) and interview questions soliciting barriers and facilitators will contain exploratory probes based on scores. For example, for patients/participants scoring low on comprehension, “What were some barriers in the communication process that may have made it difficult understand concepts in the Meaning-in-Life Counseling Program?”.

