### Data analysis plan (by objective)

Counseling completion rates will be calculated; we will treat each interpreting arm (RSMI, RCMI) as a single stage design and will assess each separately for feasibility (*primary outcome*). We will calculate frequencies and percentages to summarize recruitment, randomization, retention, acceptability (*secondary outcome*), and usability across all 3 arms (RSMI, RCMI, and bilingual provider). Based on the calculation outlined by Khan, Sarker, and Hackshaw [58], observing 11 or more successes out of 15 in a given arm would allow us to be sufficiently confident that the population feasibility of the corresponding interpretation mode is 90% against a null of 40%. In our calculations, we have set our statistical power to 90% and our Type I error rate to 0.025 to reduce the chance of false discovery. This provides us with sufficient combined statistical power, assuming the two tests are independent.We will summarize (1) therapeutic alliance scores and MCP-Ch content comprehension at T4 across all 3 arms (RSMI, RCMI, and bilingual provider) and (2) number and nature of clinically significant interpreting errors in MCP-Ch Session 1 across the interpreting arms (RSMI, RCMI) (*secondary outcomes*). We will also summarize treatment credibility/expectancy at T2 and differences in post- vs. pre-intervention distress, spiritual well-being, quality of life, anxiety and depression, meaning-in-life, hopelessness by arm (*exploratory outcomes*). These descriptive summaries by arm will provide preliminary indications of whether delivery of psycho-oncology counseling via RSMI or RCMI may potentially achieve clinically significant benefits, which will aid in the design of, and be further assessed in, a subsequent fully powered trial [29]. We will assess baseline contextual factors at T1 (e.g., digital health care literacy, level of English proficiency) to examine whether therapeutic alliance and MCP-Ch content comprehension scores differ by these variables. We will use an error analysis tool developed by Gany et al. [21] to obtain the number and nature of clinically significant errors in MCP-Ch Session 1. Specifically, a panel of 2–4 psycho-oncology clinicians blinded to the interpreting method (i.e., RSMI or RCMI) will review and code transcripts. They will independently code each script to identify clinically significant content and meet to reconcile any differences in their selection of clinically significant content. Examples of potentially clinically significant content include history of cancer diagnosis, past psychiatric history, MCP-Ch session exercises, and plans for future visits. Once all clinically significant content has been identified, a second blinded panel of 2–4 bilingual coders will independently code clinically significant content to identify interpreting errors, yielding a total count of clinically significant interpreting errors. To ensure rigor, coders on both panels will first separately conduct preliminary analyses on a subset of transcripts using the described protocol. Interrater reliability will be assessed by calculating percent agreement. Consensus meetings will be held to adjudicate disagreements and refine error categories and the analytic approach as needed until strong interrater reliability is reached (i.e., *k* = 0.80), at which point coders will commence coding of the remaining transcripts.To assess our semi-structured interviews with “extreme responders,” we will use thematic content analysis [59] to derive insights directly from participants’ narratives, following established guidelines for conducting rigorous qualitative research [60]. First, coders will each read a subset of interviews and develop codes to characterize responses. Coders will then meet to establish an initial codebook, which will be used to code the remaining interviews. Regular consensus meetings will be held to confirm the reliability of coding. The codebook will be iteratively revised as new codes emerge, and codes will be summarized into themes. Prominent themes will include those observed across the majority of interviews as well as key divergences between sub-groups. Findings will be integrated using NVivo [61], which enables qualitative and quantitative data to be paired by participant and in summary format. The coded qualitative data will be explored in relationship to participant outcomes, baseline characteristics, contextual factors, and study arm to further elucidate barriers and facilitators to the implementation of remote interpreting in the psycho-oncology setting.

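### Score-dependent interview probes, with a leading example for low comprehension scorers, may partly create the link between low scores and communication barriers that the analysis then looks for

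*Protocol article*

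**What the plan says.** Under Qualitative interviews (T9), the protocol article states that "selection of patients/trial participants will be guided by quantitative results", namely low versus high therapeutic alliance, comprehension and acceptability. The same sentence continues that "interview questions soliciting barriers and facilitators will contain exploratory probes based on scores". One example follows. It is meant for those with a low comprehension score and reads: "What were some barriers in the communication process that may have made it difficult understand concepts in the Meaning-in-Life Counseling Program".

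The section also describes what is common to all interviews: "Interviews will be conducted by study staff using a semi-structured guide with the following domains". The first domain is general feedback. The second is barriers and facilitators, covering interpreter-mediated communication, the growth of the alliance, and delivery of the intervention. Neither domain is restricted by score.

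Under Data analysis plan (by objective), the part on the third objective says that thematic content analysis will be used to "derive insights directly from participants’ narratives". It adds: "Prominent themes will include those observed across the majority of interviews as well as key divergences between sub-groups". It ends with the integration step: "The coded qualitative data will be explored in relationship to participant outcomes, baseline characteristics, contextual factors, and study arm".

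**The concern.** Patients are chosen for interview by their scores, probed according to those scores, and then compared on their coded answers by those scores. If the probe given to low scorers suggests an answer, that answer can turn up more often among low scorers for that reason alone. The comparison of codes with outcomes cannot separate this from a real difference in what patients experienced.

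The third objective uses these interviews to put the quantitative results in context and to inform best practice for interpreter-mediated counselling. A theme that low comprehension goes with communication barriers would be a natural headline for that objective. If the wording helped to produce it, other reasons for a low comprehension score, such as illness, fatigue, education or the counselling material itself, could be under-reported, and advice on interpreting could rest on less evidence than it seems to.

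**Working it through.** No figure in the document bears on this point, so there is none to reproduce. The check sets four statements side by side.

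1. **Who gets which probe.** The T9 section makes the probes depend on the score. The variables are alliance, comprehension and acceptability, the same three that guide selection.

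2. **What the printed probe presumes.** It has two parts. The opening asks which barriers there were in the communication process; this presupposes that some existed and names a single domain. The second part says that they *may* have made understanding difficult, which leaves the causal step open. The question is therefore leading about the existence and the kind of barrier, and tentative only about the effect. It offers no opening for a cause outside communication.

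3. **What is done with the answers.** The analysis plan relates codes to participant outcomes. Comprehension, alliance and acceptability are among those outcomes, so the variable that sets the probe is also one on which the answers are compared. Divergences between sub-groups are then reportable as prominent themes.

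4. **What would separate prompted from spontaneous content.** The article describes no distinction between a barrier that a patient raised unasked and one named in reply to a score-based probe. It says that insights come directly from patients' narratives, which fits an unprompted mention better than a prompted one.

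Taken together, these allow an association between low score and barrier code to arise partly from the interview.

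**Illustration only; every value is assumed.** Let *b* be the share of patients who mention a communication barrier without a leading probe, the same at all scores. Let *u* be the share of the remaining patients from whom a prompt draws a mention. The expected share with a barrier code is then *b* + (1 − *b*) × *u*.

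- With *b* = 0.30 and *u* = 0.20 in low scorers: 0.30 + 0.70 × 0.20 = 0.44.
- With *b* = 0.30 and *u* = 0.50 in low scorers: 0.30 + 0.70 × 0.50 = 0.65.
- High scorers with no comparable prompt (*u* = 0): 0.30. The apparent gap is 0.44 − 0.30 = 14 to 0.65 − 0.30 = 35 percentage points, with no true difference.
- High scorers prompted by the common domain with *u* = 0.20, low scorers at *u* = 0.50: 0.65 − 0.44 = 21 points.
- Both groups prompted equally: 0 points.

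On these assumptions the artefact runs from nothing to 35 points. What drives it is the difference in prompting between score groups, and the document does not give that difference.

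**The case against.** The strongest reply is that tailoring is the purpose of the design. The trial is explanatory sequential: interviews follow up extreme scores in order to explain them, and the qualitative and quantitative data are deliberately paired by participant. The second domain asks everyone about barriers and facilitators, and the score-based probes sit inside those questions rather than replacing them. The full interview guide is not shown; it may already open with neutral questions. The plan speaks only of exploring codes in relation to outcomes. It also examines comprehension and alliance against baseline factors, interviews interpreters and interventionists, and has Session 1 interpreting errors coded by blinded panels, so the patient interviews are not the only evidence on interpreting.

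Much of this stands, and it rules out several stronger readings.

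- A reader might infer that high scorers are never asked about communication barriers. The article does not say so. It prints one example, for low scorers, and shows no probe for high scorers.
- A reader might say that the probe tells patients that communication made understanding difficult. The wording is conditional on that step; what it presupposes is that barriers existed.
- A reader might take the plan to claim that the interviews show interpreting to be the cause of low scores. It makes no such claim.
- A reader might want scores withheld from coders and all probe answers kept out of the integration. That is a debatable trade-off in a design that pairs data by participant, and the point does not need it.

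The reply does not remove three facts, all in print: the probes differ by score, the example chosen to illustrate them is leading, and the coded answers are compared by score. Following up extreme scores is legitimate. The weakness is the combination of leading, score-specific wording with a later comparison on the same score.

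**Conclusion.** The point holds in a limited form. Followed as printed, the plan allows an apparent link between low scores and communication barriers to be partly a product of question wording. The conclusion rests on the printed example being representative of the score-based probes, and on prompted answers being coded together with spontaneous ones; the article says nothing to the contrary on either.

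The direction is clear but the size is not known. The figures above show how the effect depends on unequal prompting and are not an estimate for this trial. The common barriers-and-facilitators domain may make the effect small.

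The consequence is confined to what the third objective can conclude. The feasibility outcome and the traffic-light progression criteria do not depend on the interviews. This is a worthwhile, nearly free improvement, not a fault that threatens the trial.

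**What to change.** 1. Reword the example probe so that it presumes no cause, for instance: what helped you to understand the programme's concepts, and what made it harder?
2. Put that same open question to every patient, in all three arms and at every score, before any score-based probe. If the guide already does this, say so in the article or its supplement.
3. Keep the tailored probes, placed after the open question and worded in the same neutral way.
4. Tag each mention in NVivo as prompted or unprompted.
5. When codes are compared by score or sub-group, report unprompted mentions separately and base the comparison mainly on them. Use the answers to probes as explanatory material.

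The cost is a small revision of the interview guide, one extra tag in coding, and perhaps a few more minutes per interview. Enrolment began in March 2024, so some interviews may already have been held; these should be labelled by the guide version used.
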